### Statistical analysis plan

Primary outcome: Characteristics of the hospitals and patients will be summarized by group of randomization. Continuous variables will be described using means with standard deviations (SD) or medians with quartile ranges. We will check for imbalances between the control and intervention groups. Differences in continuous variables will be assessed using t-tests or non-parametric tests (Wilcoxon signed rank test) whichever is appropriate. Categorical variables will be described using numbers and percentages. Differences will be assessed using chi-square tests or Fisher’s exact tests. A *p*-value lower than 0.05 will be considered a statistically significant difference. We will determine the crude rate of SAEs for the control and intervention period. Data will be analyzed according to the intention to treat principle. Additionally, a per-protocol analysis will be performed based on whether the patients’ case was discussed in a preoperative MDT meeting or not. Differences in SAEs will be analyzed using a generalized linear mixed model (GLMM), with a random effect for hospital (accounting for the clustering), adjusted for the size of the hospital (used in the constrained randomization), and for the possible confounding effect of the calendar period. The result will be expressed as the risk difference and odds ratio with the appropriate 95% confidence intervals. In case there will be differences in prognostic variables in the control and intervention group, these potential confounding variables will be added to the GLMM model. Results for unadjusted (except for clustering effect, calendar time, and size of hospital) and adjusted (by potential confounding variables) will be reported. Secondary outcomes: Analyses of the secondary outcomes for categorical variables will also be performed using GLMM, in a similar model as the one used in the analysis of the primary outcome, with adjustment for other variables if indicated. In case of counts, such as the number of SAEs, GLMM will be used assuming a Poisson-dependent variable. These results will be reported as adjusted relative risk to summarize the difference between the control and intervention periods. For numeric outcome variables linear mixed models with adjustment for other variables will be used. The MDT meeting’s execution may be refined over time. Therefore, time-by-treatment effect interactions will also be analyzed. Subgroup analyses: The study will execute exploratory subgroup analyses based on factors such as age (< 70, ≥ 70 years), size of the hospital (small vs large), and intent of surgery (life-extending, functional, palliative, relief of pain or other complaints, other). Data analysis: Data analysis will be performed using the software package IBM SPSS Statistics, version 28 for Citrix (SPSS, Inc., Chicago, IL, USA) and R statistical language (https://www.r-project.org). All structured interviews will be audio recorded and transcribed verbatim. The transcripts will be analyzed by two independent coders, using thematic inductive analysis. Coders will meet on several occasions to compare their findings and differences will be discussed until consensus is reached.

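### Covariates for the adjusted SAE model are chosen by control-versus-intervention differences, checked with tests that ignore hospital and period (one of them a paired test); fix the list in advance and say which model is primary

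*Protocol article*

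**What the plan says.** All of this stands in one paragraph of the protocol article, under Statistical analysis plan (primary outcome).

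- Purpose of the comparison: "We will check for imbalances between the control and intervention groups".
- Continuous variables: "Differences in continuous variables will be assessed using t-tests or non-parametric tests (Wilcoxon signed rank test) whichever is appropriate".
- Categorical variables: "Differences will be assessed using chi-square tests or Fisher’s exact tests".
- Threshold: a p-value "lower than 0.05 will be considered a statistically significant difference".
- Fixed part of the SAE model: this GLMM is specified "with a random effect for hospital (accounting for the clustering), adjusted for the size of the hospital (used in the constrained randomization"). Calendar period is a further fixed term, listed there as a potential confounder.
- Rule for further covariates: "In case there will be differences in prognostic variables in the control and intervention group, these potential confounding variables will be added" to that GLMM.

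Results are to be reported both with the fixed terms only and with the added covariates. The paragraph does not say which of the two is the primary analysis.

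**The concern.** There are three faults in what is stated.

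1. **The tests do not fit the design.** The outcome model carries a hospital effect and calendar period, and the Sample size section assumes an ICC of 0.1. The tests that feed covariates into that model have neither term. They treat about 1120 patients as independent, and they compare groups that were recruited at different times.
2. **One test is for the wrong data structure.** The signed rank test needs paired observations. Under Design, each patient belongs to phase 1 or to phase 2, so no pairs exist. The rank test for independent groups is the rank-sum test.
3. **The selection criterion is the wrong one.** Whether a variable differs between phases says nothing about how strongly it predicts SAEs. Strong predictors that happen to balance are left out. Prognostic variables that differ only through hospital mix or drift over time are let in.

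At stake are the precision and the credibility of the adjusted estimate, whose content is not known until the data are seen. Adjustment is reasonable in this trial. Entry rests partly on clinical doubt (Study population), and patients are recruited after the hospital's phase is known (Design, Recruitment), so case mix could shift at crossover. A shift of that kind is not removed by period terms.

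**Working it through.** **Inputs from the protocol article.** 14 hospitals in 7 blocks of 2 and 8 periods of 3 months (Design, Fig. 1 legend); 10 patients per hospital per period (Recruitment); 43% versus 27.5%, ICC 0.1, CAC 0.8, t-distribution, two-sided 5%, 87% power (Sample size).

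**Assumptions not in the documents.** The ICC of a baseline covariate (shown from 0.01 to 0.10), CAC 0.8 for covariates (borrowed from the outcome), equal cell sizes, and 10 independent covariates for the multiplicity illustration.

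**Step 1: the plan's own figure.** N = 14 × 8 × 10 = 1120. With fixed period effects, the average of the two binomial variances and a nested exchangeable correlation (ICC 0.1, CAC 0.8), the standard error is 0.0494. The degrees of freedom are 112 − 8 − 14 = 90, and power is 87.4%. The stated 87% reproduces. With decay of 0.8 per period, power is 79.4%. The nested structure is therefore used first below and per-period decay is the alternative.

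**Step 2: group sizes and timing.** The two hospitals in sequence s (s = 1 to 7) have s control periods and 8 − s intervention periods. Control cells: 2 × (1 + … + 7) = 56. Intervention cells: 112 − 56 = 56. This gives 560 versus 560 patients. The mean control period is Σ s(s+1)/2 ÷ 28 = 84/28 = 3. The mean intervention period is (7 × 36 − 84)/28 = 168/28 = 6. Intervention patients enter on average 3 periods (9 months) later.

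**Step 3: true versus assumed variance of the raw difference.** Each cell mean has weight ±1/56. For a covariate with unit variance and ICC ρ:

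- Nominal variance assumed by the test: 2/560 = 1/280.
- Cell-level part: 112/56² × [(1 − ρ)/10 + 0.2ρ] = (1/28) × [(1 − ρ)/10 + 0.2ρ].
- Hospital-level part: 0.8ρ × Σ(8 − 2s)²/56², summed over hospitals = 0.8ρ × 224/3136 = 0.8ρ/14.
- Ratio to nominal: 280 × (sum of the two parts) = (1 − ρ) + 2ρ + 16ρ = 1 + 17ρ.

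**Step 4: chance that a nominal 5% test flags a covariate with no true difference and no trend**, 2 × [1 − Φ(1.96/√ratio)]:

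| Assumed covariate ICC | Ratio, nested | Flagged | Ratio, per-period decay | Flagged |
|---|---|---|---|---|
| 0.01 | 1.17 | 7% | 1.21 | 7.5% |
| 0.05 | 1.85 | 15% | 2.05 | 17% |
| 0.10 | 2.70 | 23% | 3.09 | 26.5% |

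**Step 5: several covariates.** With 10 independent null covariates at ICC 0.05 (nested), the chance of at least one flag is 1 − 0.85¹⁰ = 80%. At a true 5% level it is 1 − 0.95¹⁰ = 40%.

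**Step 6: drift.** Because of the 3-period gap, a drift in case mix of 0.02 SD per period gives a raw difference of 0.06 SD. Such a covariate is flagged 17% of the time at ICC 0 and 34% at ICC 0.10 (per-period decay). The period terms in the outcome model already absorb a trend common to all hospitals, so these flags mostly do not point to confounding.

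**The case against.** **A fixed model is already there.** The GLMM with hospital, hospital size and period is specified in advance and reported beside the adjusted one. This stands. A reader might infer that the trial has no pre-specified primary analysis, or that the SAE result as a whole is data-driven. The text does not support that. What remains is that neither model is named as primary.

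**The p-value trigger is inferred.** No single sentence says that p<0.05 decides entry, and only prognostic variables are eligible. Both points are correct. The p<0.05 reading is the natural one, because the imbalance check, the tests, the threshold and the inclusion rule share one paragraph and no other criterion is given. On any reading, inclusion still depends on whether the groups differ.

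**A false flag is not a biased treatment effect.** This also stands. A reader might infer from the flag rates that the effect estimate is biased or its Type I error inflated. In a simulation of the 10-covariate scenario (ICC 0.05, nested CAC 0.8, outcome ICC 0.1, continuous outcome, known correlation, no drift, 3000 runs), at least one covariate was flagged in 81% of runs. The selected model still showed no detectable bias and 4.1% Type I error, against 4.6% with no covariates and 4.6% with all of them. The visible loss was precision: a standard error about 8% larger than with full adjustment, a figure that depends on the assumed covariate strengths.

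**A covariate list belongs in the statistical analysis plan.** Its absence from a condensed article is not the fault raised here. The fault is the selection rule that the article states.

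**The signed rank test is a naming slip.** Probably so, and it would not alter the SAE result. It is still a wrong statement and needs correcting.

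**Conclusion.** The point holds, within limits. The article states a selection rule that rests on tests with the wrong error rate for this design, and it names a paired test for unpaired groups. For a covariate with no true difference, the nominal 5% becomes about 7% to 23% under the correlation structure that reproduces the stated power, and 7.5% to 26.5% under per-period decay. The covariate ICCs are assumptions; the rate exceeds 5% at every positive value shown.

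The consequence is limited to the adjusted SAE estimate, which is defined only after the data are seen and loses precision when strong predictors happen to balance. The main uncertainty left for the primary conclusion is which of the two reported models carries it. The rule should be changed, but it does not invalidate the primary analysis and leaves the sample size untouched.

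**What to change.** Rewrite the paragraph so that it:

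1. describes baseline characteristics by phase, without significance tests;
2. drops the rule that adds variables because the groups differ;
3. defines the adjusted model in advance, adding prognostic variables the trial already records (age, ASA class and Clinical Frailty Scale from the entry criteria, and intent of surgery from the planned subgroups) to the hospital, hospital-size and period terms already fixed;
4. states which of the two models is primary;
5. names the rank-sum test wherever a rank test of independent groups is kept.

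The cost is one rewritten paragraph and a few more model parameters. No new data are needed and no sample-size figure changes.

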### Recruitment

Consecutive high-risk noncardiac surgical patients will be assessed for potential eligibility at the preoperative assessment by the anesthesiologist and asked to participate if they fulfill the inclusion criteria. Eligible patients will receive written and video information about the study. Written informed consent will be obtained by a trained (research) nurse or a physician before surgery (control; phase 1) or before the MDT meeting (intervention; phase 2). To facilitate the inclusion of patients with limited health literacy in our study, we incorporated measures to guarantee that information about the study, questionnaires, and informed consent were written at a suitable language level (level B1).

Each hospital is estimated to include ten patients on average per 3 months. As hospitals vary in size and do not serve the same number of surgical patients, each hospital includes a different number of patients during each period of 3 months. Patients can withdraw consent at any time for any reason if they wish to do so. Data from patients who withdraw will be used in the analysis until the date of withdrawal, unless the patient states otherwise.

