
### Sample size

Statistical analysis determined that a sample size of 14 clusters, or around 1120 patients, would be needed to identify a 15.5% decrease in clinically significant SAEs (Clavien-Dindo ≥ 3). The results showed that this sample size would achieve 87% power with a two-sided test at a 5% significance level. These calculations were based on pilot data that showed a 43% adverse event rate in the control group and a 27.5% rate in the intervention group [5]. We used the Shiny CRT calculator: https://clusterrcts.shinyapps.io/rshinyapp to calculate the sample [38]. No literature is available to guide potential values of the period intra-cluster coefficient (ICC). We assumed that the outcomes of different patients from the same hospital would not change over different periods, apart from the difference in the control condition period and the MDT meeting period. However, we chose a non-exchangeable correlation structure (with a two-period decay) in our sample size calculation to consider an unexpected decline. For the ICC, we used a moderate value of 0.1, and for the cluster auto-correlation (CACs), a value of 0.8. Lower values of the ICC lead to a higher power. Furthermore, we used the T-distribution as we have relatively small samples. We expect an average of 20 new high-risk noncardiac patients in each block. We assume that no correlation exists between hospitals. As we expect patients to drop out we will include 1200 patients in this study (± 7% dropout = 1120).

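### The SAE count is tied to a Poisson model with no allowance for differences between patients, so its interval may be too narrow if affected patients average about 1.5 or more SAEs

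*Protocol article*

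**What the plan says.** The Statistical analysis plan section gives the primary SAE analysis as a generalized linear mixed model "with a random effect for hospital (accounting for the clustering), adjusted for the size of the hospital" and for calendar period. Categorical secondary outcomes are to be analysed "in a similar model as the one used in the analysis of the primary outcome, with adjustment for other variables if indicated". For counts the text commits to a distribution: "In case of counts, such as the number of SAEs, GLMM will be used assuming a Poisson-dependent variable". It then says: "These results will be reported as adjusted relative risk".

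The count sentence lists no random effects of its own. It names no dispersion term, negative binomial model, patient-level random effect or robust variance. It also names no exposure term, although the Recruitment section says: "Data from patients who withdraw will be used in the analysis until the date of withdrawal".

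The Sample size section supplies the only event rates: "pilot data that showed a 43% adverse event rate in the control group and a 27.5% rate in the intervention group". The documents give neither a number of SAEs per patient nor a variance for the count.

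**The concern.** Under a Poisson GLMM, patients with the same covariates in the same hospital and period have counts whose variance equals their mean. A hospital random effect moves the mean of a whole hospital. It does not loosen that constraint between patients within it.

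Two features of the trial make the constraint doubtful:
- The Outcome section counts events needing endoscopic or surgical intervention, single or multiple organ failure, and death. One patient can have several of these in sequence while most have none.
- The Introduction reports an earlier study in which 43% of high-risk patients had no surgery after the team meeting. The intervention arm may therefore mix operated and unoperated patients, who plausibly differ in SAE rate.

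If counts are overdispersed, the standard error is understated and a chance difference in the SAE count is more likely to be called significant.

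There is also a labelling problem. A log-link Poisson model estimates a ratio of mean counts or, with an exposure term, of rates. Calling that a relative risk invites confusion with the risk of having any SAE, which is the binary primary outcome.

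**Working it through.** **The plan's own figure.** There is none for the count analysis. For the binary primary outcome the plan says "this sample size would achieve 87% power with a two-sided test at a 5% significance level". With 14 hospitals, 7 sequences, 8 periods, 10 patients per hospital-period, 43% against 27.5%, ICC 0.1 and CAC 0.8, a block-exchangeable correlation and t on 90 df, I get 87.4%. That calculation does not involve the count model.

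**Inputs.** The 43% and 27.5% come from the Sample size section and are read here, as an assumption, as the share of patients with at least one SAE. SAEs per affected patient are assumed over 1.0 to 2.5, the same in both arms. The design has 28 control and 28 intervention periods over its seven sequences, so the arms are taken as equal in size.

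**What Poisson implies.** If P(0) = 1 − p, the mean is −ln(1 − p), and SAEs per affected patient are −ln(1 − p)/p:
- control: 0.562/0.43 = 1.31
- intervention: 0.322/0.275 = 1.17

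**Formulas.** Let φ = variance/mean in an arm and m its mean count. For the log ratio,

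(true SE / Poisson SE)² = (φ₀/m₀ + φ₁/m₁) / (1/m₀ + 1/m₁).

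With r the SE ratio, coverage is 2Φ(1.96/r) − 1 and the relative interval error is 1 − 1/r.

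**Model A: one SAE plus Poisson(λ) further SAEs among affected patients.** Here m = p(1 + λ) and φ = λ/(1 + λ) + (1 − p)(1 + λ). For example, at λ = 0.5:
- φ₀ = 0.333 + 0.57 × 1.5 = 1.19
- φ₁ = 0.333 + 0.725 × 1.5 = 1.42
- r² = (1.188/0.645 + 1.421/0.4125)/(1/0.645 + 1/0.4125) = 1.33, so r = 1.153

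| SAEs per affected patient | φ control / intervention | r | Coverage |
|---|---|---|---|
| 1.0 | 0.57 / 0.72 | 0.815 | 98.4% |
| 1.2 | 0.85 / 1.04 | 0.982 | 95.4% |
| 1.3 | 0.97 / 1.17 | 1.046 | 93.9% |
| 1.5 | 1.19 / 1.42 | 1.153 | 91.1% |
| 2.0 | 1.64 / 1.95 | 1.352 | 85.3% |
| 2.5 | 2.03 / 2.41 | 1.504 | 80.8% |

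φ passes 1 at about 1.33 SAEs per affected patient in control and 1.17 in intervention.

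**Model B: negative binomial with shape k.** Here m = k[(1 − p)^(−1/k) − 1] and φ = 1 + m/k.

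| k | m control / intervention | φ control / intervention | r | Too narrow by | Coverage |
|---|---|---|---|---|---|
| 2 | 0.65 / 0.35 | 1.32 / 1.17 | 1.108 | 9.7% | 92% |
| 1 | 0.75 / 0.38 | 1.75 / 1.38 | 1.227 | 18.5% | 89% |
| 0.5 | 1.04 / 0.45 | 3.08 / 1.90 | 1.503 | 33.5% | 81% |

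Model B is overdispersed by construction, so it shows size only and says nothing about direction. Model A can go either way.

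**Simulation under no effect.** The layout was 14 hospitals × 8 periods × 10 patients. A Poisson GLM with fixed hospital and period effects stood in for the GLMM. Under Model A (43% affected in both arms, 600 runs per scenario), two-sided type I error was 1.0% at 1.0 SAE per affected patient, 4.2% at 1.3, 7.3% at 1.5, 10.7% at 2.0 and 15.2% at 2.5. Under Model B it was 9.3%, 13.7% and 27% for k = 2, 1 and 0.5. Scaling the variance by the Pearson dispersion brought it to about 4 to 6% throughout.

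**Label.** The ratio of risks is 27.5/43 = 0.64. With the same risks, Model B gives ratios of mean counts of 0.349/0.649 = 0.54 (k = 2) and 0.451/1.039 = 0.43 (k = 0.5). The two quantities need not agree.

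**The case against.** The strongest reply is that this is a condensed article. A full protocol exists on request, and dispersion checks, fallback models and offsets commonly sit there or in a separate analysis plan. That stands as far as missing detail goes, and silence about a check is not the point here. The point is that the article does state a distribution, and the one it states is a fragile choice for this outcome.

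Second, a reader might infer that the interval will be too narrow. The documents do not support that. They give no SAEs per patient, and low multiplicity is possible because death is itself an SAE and ends the count. At 1.0 to 1.2 SAEs per affected patient the Poisson interval is about right or too wide. This part of the objection stands in full.

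Third, the hospital-only structure is stated for the primary model, and similarity to that model is said of categorical outcomes. For counts it is an inference. Nor do the documents name a hospital-by-period random effect in any model, so none should be assumed in the remedy.

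Fourth, the consequences are limited. The number of SAEs is given as an example of a count and is not itemised among the secondary outcomes. Expected dropout of about 7% limits the effect of a missing offset. A reader might also infer that cost per SAE prevented is affected. The Economic evaluation section quantifies that uncertainty by bootstrap, not from a Poisson standard error, so the inference is not supported.

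**Conclusion.** The concern holds conditionally. The plan fixes a Poisson distribution for the SAE count and states nothing that relaxes the equality of variance and mean between patients in the same hospital and period. Whether this harms inference depends on a quantity the documents do not report. The error becomes clear from about 1.5 SAEs per affected patient, and overdispersion is plausible here but not established.

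These sizes rest on reading 43% and 27.5% as the share with at least one SAE, on assumed count distributions, on equal arms, and on fixed hospital effects in the simulations. The effect is on the standard error of a secondary analysis. The primary binary analysis and the sample size are untouched. The relative-risk label should be corrected in any case.

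**What to change.** For SAE counts, replace the plain Poisson assumption with an approach that does not force variance to equal the mean, and fix it before results are seen. Options are a negative binomial mixed model, a Poisson mixed model with a patient-level random effect, or a dispersion-scaled or robust variance. With 14 hospitals, a robust variance needs a small-sample correction. The first two options only widen the Poisson variance. A scaled or robust variance also handles counts that vary less than Poisson, which matters if most affected patients have a single SAE.

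Include log follow-up time as an offset so that withdrawn patients contribute only their observed time, and state how time after death is treated. Report the result as a rate ratio.

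The cost is a few lines of plan text and slightly more analysis work, with no new data, in the R software already named. The interval may be wider. If counts are in fact close to Poisson, the result should barely change.

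### The exploratory age subgroup is cut at 70 with no continuous age-by-MDT term; if the effect changes gradually with age, the cut loses information that a continuous term would keep

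*Protocol article*

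**What the plan says.** Under Statistical analysis plan, the protocol article bases its subgroup analyses on "factors such as age (< 70, ≥ 70 years), size of the hospital (small vs large"). Intent of surgery is the other factor named. The analyses are labelled exploratory and the list is open-ended.

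The same section sets out the model for the primary outcome: "Differences in SAEs will be analyzed using a generalized linear mixed model (GLMM), with a random effect for hospital", adjusted for hospital size and calendar period. The only treatment interaction it names concerns time: "time-by-treatment effect interactions will also be analyzed". It mentions no interaction of treatment with age, whether continuous or in two groups, and does not say why 70 was chosen.

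Age is an eligibility item under Study population, so it is available for every patient. No mean, SD or share under 70 is given anywhere.

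**The concern.** The article fixes the form and the cut-point of the age analysis, so this is a stated choice and not a detail left open. Patients must have ASA 3 or higher and a Clinical Frailty Scale of 4 or higher. Many may therefore be over 70, which would leave a smaller younger group and one broad older group in which a 71-year-old and a 90-year-old count as the same.

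If the benefit of MDT discussion rises or falls gradually with age, a two-group comparison discards the variation within each group, and the answer depends on one threshold. The trial is sized for its main effect. Any test of effect modification starts from less information than that, so a further loss matters more there. What is at stake is the precision of one exploratory question, not the trial's main conclusion.

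**Working it through.** **The plan's own figure.** The article gives no figure for the age analysis. Its only related figure is the primary power: "this sample size would achieve 87% power with a two-sided test at a 5% significance level". That figure was reproduced first, to confirm the layout used below.

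- Size: 14 hospitals × 8 periods × 10 patients = 1120.
- Event rates: "43% adverse event rate in the control group and a 27.5% rate in the intervention group", a difference of 0.155.
- Correlation: "we used a moderate value of 0.1, and for the cluster auto-correlation (CACs), a value of 0.8", with "we chose a non-exchangeable correlation structure (with a two-period decay") read as a block-exchangeable structure.
- Generalised least squares with fixed period effects and the binomial variance averaged over the two rates gives a standard error of 0.0494.
- 0.155 / 0.0494 = 3.14. With t on 112 − 8 − 14 = 90 degrees of freedom, the critical value is 1.987 and power is 0.874. This agrees with 87%.

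**Formula for the loss.** If the treatment effect changes linearly with age, the efficiency of a two-group split relative to a continuous term is the squared correlation between age and the group indicator. For normally distributed age this is

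efficiency = φ(z)² / [q(1 − q)], with z = (70 − mean)/SD and q = Φ(z), the share under 70. The loss is 1 − efficiency.

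**Results.** The means and SDs are assumptions, because the documents give none.

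| Mean, SD | z | q | φ(z)² / [q(1 − q)] | Efficiency | Loss |
|---|---|---|---|---|---|
| 70, 8 or 10 | 0 | 0.50 | 0.1592 / 0.2500 | 0.64 | 36% |
| 75, 10 | −0.5 | 0.31 | 0.1239 / 0.2133 | 0.58 | 42% |
| 75, 8 | −0.625 | 0.27 | 0.1077 / 0.1952 | 0.55 | 45% |
| 78, 10 | −0.8 | 0.21 | 0.0839 / 0.1670 | 0.50 | 50% |
| 78, 8 | −1.0 | 0.16 | 0.0585 / 0.1335 | 0.44 | 56% |

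Over mean 70 to 78 and SD 8 to 10, the loss is therefore 36% to 56%, with 16% to 50% of patients under 70.

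**Check in the trial's layout.** The calculation was repeated with patient-level ages in the stepped-wedge layout above, SD 10. The losses were about 35%, 40%, 42% and 50% at mean ages 70, 74, 76 and 78. The formula gives 36%, 40%, 44% and 50%.

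**Other assumed distributions.** Uniform 50 to 90: 25%. Uniform 55 to 95: 30%. Two left-skewed shapes with mean 73: 32% and 36%. Normal with mean 80 and SD 8: 65%.

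**What the loss means.** At 36%, 1120 patients inform the linear interaction like 1120 × 0.64 = 717. At 56%, they do so like 1120 × 0.44 = 493. Take an interaction that a continuous term would detect with 80% power, so that its expected test statistic is 1.96 + 0.84 = 2.80. With the split, power becomes Φ(√0.64 × 2.80 − 1.96) = 61% or Φ(√0.44 × 2.80 − 1.96) = 46%. The 80% is a reference point for comparison. The article makes no power claim for this analysis.

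**The case against.** The strongest case against the point is that it criticises an openly exploratory example in a condensed article. A reader might infer that age will be analysed solely in two groups. The text does not say that: the list is introduced as examples, and a continuous term is not excluded. How an exploratory subgroup is modelled is also often settled in a full analysis plan, which is not shown here, and a reason for 70 may be given there. A cut fixed in advance at least avoids a threshold chosen from the data.

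The size of the loss is open to challenge as well. It needs an assumed age distribution and a linear change of effect. If the effect really steps at 70, the split loses nothing and the linear term is the less efficient choice.

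Most of this stands as a limit on size and certainty. It does not remove the point. The article does state a specific form and cut-point, so the choice can be assessed. Every age distribution tried gave a loss of at least a quarter under a linear change. A step at 70 is covered by the spline check and by keeping the split in the report.

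**Conclusion.** The point holds as a low-priority improvement. Under a roughly linear change of effect with age, the cut at 70 loses about 36% to 56% of the information on the age-by-MDT interaction if age is normal with mean 70 to 78 and SD 8 to 10. Across the other distributions tried, the loss runs from about 25% to 65%. None of these percentages is a property of the trial as documented, because no age distribution is given.

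Two stronger readings are not supported. One is that the cut is known to discard a fixed share of the information: the loss is zero for a true step at 70 and otherwise depends on the ages actually recruited. The other is that the trial's main result is weakened: the primary model, the 1120 patients and the 87% power do not involve this split.

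**What to change.** In the analysis plan, before the data are analysed, prespecify an age-by-MDT interaction with age as a continuous variable in the planned mixed model. Use a linear term with a spline check, and make this the exploratory test of effect modification by age. Keep the results below 70 and from 70 upwards for display.

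The cost is a sentence in the plan and one model term, with no new data, patients or visits. The downside is small: one added assumption, linearity, which the spline check and the retained split address. The primary analysis, sample size and power stay as they are.
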